## Introduction

### Background

Diagnostic errors (defined as missed, delayed, or wrong diagnoses) in primary care affect an estimated 1 in 20 US adults every year [1]. About half of these errors can lead to serious preventable harm, but few interventions have been developed and tested to reduce diagnostic errors in real-world ambulatory care settings such as primary care or urgent care clinics [1-4]. This significant gap in clinical practice carries tremendous public health implications. Most individuals receive care in ambulatory care settings [5]. Diagnosis is particularly challenging in primary and urgent care because of 2 structural factors: (1) the short time duration and pressure to complete visits affects cognition and (2) primary care encompasses the broadest range of clinical concerns, from common diseases to rare conditions [6].

In current usual practice, clinicians at primary care and urgent care clinics commonly diagnose patients independently without collaboration or consultation with other health professionals or the use of health information technology (IT), potentially leading to an increased risk of diagnostic errors [7]. In focus groups about outpatient diagnosis, clinicians identified the use of technology to improve communication among them as a key strategy to enhance timely and accurate diagnosis [8]. In its recent report on diagnostic error, the National Academy of Medicine suggested that health systems employ 2 key strategies that are essential to reducing diagnostic error in the ambulatory care setting: (1) enhance interclinician collaboration and (2) develop and utilize health IT innovations in the diagnostic process [6]. A collective intelligence technology platform could be a promising tool to implement these 2 key strategies.

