### Outcomes and Measurements

#### Primary and Secondary Outcomes

Our primary outcome will be self-reported diagnostic confidence as measured by response to the survey question in the postvisit questionnaire that asks participants after reviewing the collective intelligence output for cases randomized to the intervention group: “How confident do you feel about your diagnosis for this patient?” (Not at all, somewhat, moderately, and very). We chose this outcome based on previous literature in diagnostic safety suggesting that diagnostic confidence plays an important role in medical management, evolves over time in the process of making a diagnosis, and the ability to move diagnostic confidence may contribute to avoiding diagnostic error [18,19]. Furthermore, our preliminary studies for the proposed trial suggested that clinicians’ confidence in their clinical assessment is an important factor in their cognitive process for decision making and future approach to similar cases. We also chose this measure because it is likely the most sensitive to the impact of the collective intelligence on clinicians’ complex diagnostic decision-making process, whereas clinical outcomes such as *time to diagnosis* and diagnostic accuracy can be confounded by external health care system factors such as time to receive test results, financial incentives for diagnostic testing, and other factors. The secondary outcome will be *time to diagnosis*, defined as the interval between the time of the clinic visit from which a case with diagnostic uncertainty was identified for entry into the collective intelligence platform and the time at which the clinician will have established a diagnosis for that symptom or sign. We will ascertain the time of established diagnosis as the time at which the clinician documents the new diagnosis, the result for a confirmatory diagnostic testing becomes available, or empiric treatment was initiated. We will choose the earliest occurrence of any of these three events as the time of established diagnosis.

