#### Exploratory Clinical Outcomes

We will measure and analyze specified, additional outcomes that are relevant to the diagnostic process. We will define diagnostic accuracy as having the correct diagnosis listed in the top 3 answers of the collective intelligence output (for intervention cases) or in the top 3 of the clinician’s list of possible diagnoses collected via survey data (for control cases). In addition, we will measure the number of diagnostic tests related to the initial complaint, ordered by the clinician within 30 and 90 days of the case presentation, and the number of unexpected visits (drop-in, urgent care, or emergency room) related to the initial presentation within 14 and 30 days of the index visit. Unexpected visits have been associated with higher risk of diagnostic error [1]. We refer to these as exploratory outcomes because we expect them to be highly variable both within and between clinicians and do not know whether we will have the statistical power to analyze them. Descriptive analyses of these outcomes may generate hypotheses for future study.

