#### Electronic Health Record Chart Review for Ascertainment and Adjudication of Outcomes and Other Variables

A total of 2 study investigators will independently review the medical record 6 months after the initial presentation of the case to ascertain the final diagnosis and exclude cases with persistent diagnostic uncertainty after 6 months. We will resolve discrepancies in adjudication by consensus. Our chart review will also capture the number of comorbid conditions (based on the problem list and the 10th revision of the International Statistical Classification of Diseases billing codes entered by the clinician for the visit), the type of visit (new, returning, drop-in, or urgent care), the number of diagnostic tests related to the initial presentation ordered by the clinician within 30 and 90 days of the case presentation, and the number of unexpected visits related to the initial presentation (drop-in, urgent care, or emergency room) within 14 and 30 days of the index visit. We will use the same 2-investigator adjudication process to ascertain diagnostic tests and unexpected visits related to the initial presentation.

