#### Secondary Outcome

We will use Cox regression to compare time-to-diagnosis (T2Dx) between the intervention versus the control cases (ie, intervention status as primary predictor and T2Dx as outcome).

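### Time to diagnosis is dated at the earliest of three events, none of which has to agree with the adjudicated final diagnosis, so an early wrong label that is later corrected counts as a fast diagnosis

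*Protocol article*

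**What the plan says.** Under Primary and Secondary Outcomes, the protocol article runs time to diagnosis from the clinic visit to "the time at which the clinician will have established a diagnosis for that symptom or sign". It makes that endpoint operational in three ways. The first is "We will ascertain the time of established diagnosis as the time at which the clinician documents the new diagnosis". The other two are "the result for a confirmatory diagnostic testing becomes available, or empiric treatment was initiated". The combining rule is explicit: "We will choose the earliest occurrence of any of these three events as the time of established diagnosis".

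Under Secondary Outcome, the analysis is stated as "We will use Cox regression to compare time-to-diagnosis (T2Dx) between the intervention versus the control cases", with no condition on whether the diagnosis was correct.

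Under Electronic Health Record Chart Review, two investigators read the record at 6 months "to ascertain the final diagnosis and exclude cases with persistent diagnostic uncertainty after 6 months". The Figure 3 legend adds that record review at 6 to 9 months serves to adjudicate the secondary and exploratory outcomes.

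The Background section gives the harm that the trial addresses: "Diagnostic errors (defined as missed, delayed, or wrong diagnoses". Study Objectives names accuracy in reaching a correct diagnosis as one of the two things the platform should improve.

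**The concern.** An outcome meant to show faster diagnosis should not reward reaching the wrong one sooner. As worded, the clock stops at the first qualifying event, and a later correction cannot move that date. Two effects that matter to this trial are then hard to see:

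- An output that leads clinicians to commit earlier to wrong labels could look like a benefit.
- An output that prevents wrong first labels without changing speed would show nothing.

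A separate problem comes from the treatment event. Empiric treatment can begin with no diagnosis made. Criterion 4 under Case Selection Criteria admits cases because such treatment was given without full diagnostic certainty. For those cases the clock can stop at the index visit. Randomization comes later, once the output is available, and the clinician receives the output 60 to 80 hours after the visit. An event at the index visit cannot reflect the intervention.

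**Working it through.** **1. What the text does with one case.** Take an illustrative case with a wrong diagnosis documented on day 5, the correct one on day 70, and no earlier test result or treatment. The earliest-event rule scores it at 5 days. Dated on the final diagnosis it would be 70 days, a difference of 70 − 5 = 65 days. By the Background definition it is both wrong and delayed.

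**2. Whether another section catches it.**

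- *Exclusion at 6 months.* This removes cases still uncertain. The case above is resolved by then, so it stays in with its day-5 date.
- *Adjudication of the secondary outcome (Figure 3 legend).* This says that chart review establishes the outcome. It does not replace the earliest-event rule or say that the event must match the final diagnosis.
- *Diagnostic accuracy.* It is exploratory and defined separately: "We will define diagnostic accuracy as having the correct diagnosis listed in the top 3 answers of the collective intelligence output (for intervention cases". In the intervention arm it scores the platform's output, so it cannot show whether clinicians documented wrong labels early.
- *Before-and-after accuracy (Exploratory Analyses).* This is confined to intervention cases and does not alter the time-to-diagnosis date.

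**3. Possible direction of the bias.** The documents give no figure to reproduce and none of the inputs below, which are all assumed. The simulations model the documentation event only, unless stated.

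*Illustration A.* First documented diagnosis: exponential, mean 20 days in control. Wrong first labels: 20% in control, corrected after a further exponential time of mean 60 days. Censoring at 180 days; 100,000 cases per arm; Cox model.

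Mean time to the correct diagnosis, before censoring = mean time to first label + (share wrong × 60). In control this is 20 + 0.20 × 60 = 32 days.

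| Intervention effect assumed | Mean to correct diagnosis | HR, first documented diagnosis | HR, correct diagnosis |
|---|---|---|---|
| Same speed, wrong labels 10% | 20 + 0.10 × 60 = 26 | 1.00 | about 1.18 |
| Mean 16 days, wrong labels 30% | 16 + 0.30 × 60 = 34 | about 1.25 (20/16 = 1.25) | about 0.97 |

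In the first row a real gain of 32 − 26 = 6 days is invisible. In the second, the correct diagnosis comes 34 − 32 = 2 days later on average, yet the outcome favours the intervention.

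*Illustration B.* Time to the correct diagnosis is the same in both arms (exponential, mean 30 days). A share of intervention cases also gets an early wrong label (exponential, mean 7 days); control has none. With 330 cases per arm and 200 replicates, the hazard ratio is 0.99, 1.09, 1.19 and 1.31 for shares of 0, 10%, 20% and 30%. Restricted to the correct diagnosis it stays at 0.99 to 1.00.

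**4. Adding the treatment event.** In the second row of illustration A, let 20%, 40% or 60% of cases in both arms stop at the index visit. The hazard ratio of about 1.25 falls to about 1.19, 1.14 and 1.10. Events before randomization thus pull the comparison towards 1, whatever the intervention does afterwards.

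**The case against.** The best defence is that the protocol means the adjudicated diagnosis. It speaks of the new diagnosis and of an established one, and the Figure 3 legend places the secondary outcome under adjudication, so reviewers may be dating the diagnosis they settle on. That reading is possible, but the text does not state it. The earliest-event rule, and a treatment event that needs no diagnosis at all, point the other way.

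Speed and accuracy may also fairly be kept as separate measures. The protocol itself warns that time to diagnosis can be confounded by health-system factors, and Multiple Hypothesis Testing treats secondary results as exploratory. This stands, and it limits the weight of the point. It does not remove it, because the accuracy measure does not score what intervention clinicians documented.

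A reader might infer that a test result refuting the suspected diagnosis also stops the clock. The word confirmatory makes that strained; this route carries an implicit check, though either of the other two events can pre-empt it. A reader might also infer that the correct diagnosis never enters the outcome. That is too absolute: where the first qualifying event already concerns the correct diagnosis, the date is right.

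**Conclusion.** The point holds as a flaw in how the secondary outcome is defined. The event date need not agree with the final diagnosis. A case mislabelled and then corrected within 6 months keeps its early date, and the treatment event can stop the clock before a diagnosis exists or before randomization.

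The size cannot be derived from the documents. It depends on how often first labels are wrong in each arm, how long correction takes, and how many cases are dated by treatment, and none of these is given. It would be tempting to take the hazard ratios above as estimates of the bias. They are not: they rest on assumed inputs, most leave out the treatment event, and they show only that the outcome can favour the intervention without a gain in time to the correct diagnosis, or miss a real gain. The primary outcome, diagnostic confidence, is not affected.

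**What to change.** In the two-reviewer chart review already planned, also record the first date on which the adjudicated final diagnosis was documented by the clinician or confirmed by a test result, and analyse time to diagnosis on that date. State openly that empiric treatment alone then no longer ends the interval; this is a second change to the definition.

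Keep the present earliest-of-three measure as a supporting outcome under a plain label, such as time to first working diagnosis or treatment. Report by arm the share of first diagnoses later replaced.

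The article reports data collection complete as of June 2019. If charts are already abstracted or the outcome is locked, keep the present rule as the labelled main definition and add the concordance-based date as a sensitivity analysis.

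The cost is some extra abstraction and somewhat fewer and later events. The remedy is also partial: a wrong diagnosis never revised within 6 months may still be adjudicated as final.

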Once the collective intelligence output becomes available for a case, the study team randomizes it to the intervention or control cases. The study team assigned each case a unique study identification number for tracking purposes. Using a random number generator in blocks of four, we will randomize half of the cases, for each clinician, to an intervention group in which the clinician will receive a collective intelligence output between 60 and 80 hours from the time the clinician saw the patient in the clinic (ie, within 24-36 hours of case entry). For cases randomized to the controlled group, Human Dx will generate collective intelligence, but it will not be shared with the clinician. Clinicians will complete an online postvisit questionnaire for all of their cases (control and intervention) that provides their initial impressions of the case (eg, differential diagnosis and perceived case difficulty) and level of diagnostic confidence. The questionnaire for cases assigned to the intervention group includes additional questions that the clinician will answer after reviewing the collective intelligence output to assess the effect of the output on their diagnosis, plan, and confidence. The study scribes and the *contributors* on Human Dx will be blinded to case randomization.

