### Case Selection Criteria

Scribes will select cases based on a rubric designed to capture diagnostic uncertainty. If a case meets any of the following criteria, it will be entered into the Human Dx platform: (1) a new symptom or abnormality in laboratory, physical exam, or radiographic finding; (2) a recurrent symptom or abnormality in laboratory, physical exam, or radiographic finding without a clear diagnosis or etiology; (3) a pending diagnostic test ordered to evaluate a new or unresolved condition; (4) empiric treatment provided without complete diagnostic certainty; and (5) if the clinician submitted a request for electronic consultation from a specialist within the health network for a diagnostic or management problem. Clinicians may also flag a case for review that the scribes will enter into the Human Dx platform whether or not it meets the above rubric’s selection criteria.

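### Starting empiric treatment marks a case as uncertain at entry but as diagnosed in the time-to-diagnosis outcome, so events before randomisation count and dilute the hazard ratio

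*Protocol article*

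**What the plan says.** **Entry.** Case Selection Criteria applies an any-of rule: "If a case meets any of the following criteria, it will be entered into the Human Dx platform". The fourth criterion is "4) empiric treatment provided without complete diagnostic certainty" and the third is "3) a pending diagnostic test ordered to evaluate a new or unresolved condition".

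**Outcome.** Primary and Secondary Outcomes sets the origin of time to diagnosis at the index visit: it is "defined as the interval between the time of the clinic visit from which a case with diagnostic uncertainty was identified" up to the time a diagnosis is established. Three events establish it: the clinician documents the new diagnosis, "the result for a confirmatory diagnostic testing becomes available, or empiric treatment was initiated". The combining rule is "We will choose the earliest occurrence of any of these three events as the time of established diagnosis".

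**Timing.** Under Selection, Entry, and Randomization of Clinical Cases, scribes open the record 24 to 36 hours after the session and contributors respond within 24 to 36 hours of case entry. The case is randomised once the output exists. The clinician receives the output, in the intervention arm only, "between 60 and 80 hours from the time the clinician saw the patient in the clinic".

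**Analysis.** The Secondary Outcome part of the Analysis Plan specifies a Cox regression of this time on intervention status. The chart review section says that cases still uncertain after 6 months will be excluded.

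**The concern.** One clinical fact carries opposite meanings in two sections. At entry, empiric treatment shows that the diagnosis is open. In the outcome, it shows that the diagnosis is settled. Nothing exempts the treatment that qualified the case.

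The clock also runs for two to three days before any arm exists. A test already pending at the visit can report in that interval and be scored as the event. The intervention cannot influence any of these events, yet they enter the Cox model as full events.

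At stake is the reading of the trial's only named secondary outcome. A hazard ratio near 1 could mean that the output does not speed diagnosis, or merely that many events had already happened. The analysis as defined cannot tell these apart.

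**Working it through.** **Step 1: timeline from the article's figures (hours after the visit).**

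| Point | Time |
|---|---|
| Clock starts | 0 |
| Empiric treatment, if started at the index visit | 0, so the event is scored at about 0 |
| Scribe review | 24 to 36 |
| Output exists and case is randomised | 24 + 24 = 48 to 36 + 36 = 72 |
| Output delivered (intervention arm) | 60 to 80 (2.5 to 3.3 days) |

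For a case treated empirically at the index visit, the event precedes randomisation by about 2 to 3 days.

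**Step 2: direction of the effect.** Randomisation is within clinician and comes after these events, so their expected frequency is the same in both arms. In the Cox model they contribute information centred on a log hazard ratio of 0. Events after the output carry the true log hazard ratio. The estimate is roughly an average of the two, weighted by event counts:

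estimated log HR ≈ (1 − w) × true log HR, with w = f / [f + (1 − f)q]

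Here f is the share of cases with an event before the output, and q is the proportion of the remaining cases diagnosed by 6 months, averaged over arms.

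**Step 3: illustration.** The article gives no event rate, hazard ratio or power for this outcome, so there is no planned figure to reproduce. It gives only the case count: 33 clinicians × 20 = 660, or 330 per arm. Assumed: true HR 1.5, 70% of the other control cases diagnosed by 6 months, exponential times, administrative censoring at 6 months.

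- Intervention arm diagnosed by 6 months: 1 − 0.30^1.5 = 1 − 0.164 = 0.836. So q = (0.700 + 0.836)/2 = 0.768.
- f = 20%: w = 0.20/(0.20 + 0.80 × 0.768) = 0.246. Then 0.754 × ln 1.5 = 0.306, HR 1.36.
- f = 40%: w = 0.40/(0.40 + 0.60 × 0.768) = 0.465. Then 0.535 × ln 1.5 = 0.217, HR 1.24.
- f = 5%: w = 0.05/(0.05 + 0.95 × 0.768) = 0.064. Then 0.936 × ln 1.5 = 0.379, HR 1.46.

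Simulated trials with Cox fits agree: 1.35 at f = 20% and 1.24 at f = 40%, against about 1.5 among the cases still at risk. With a true HR of 1.25 they give 1.18 and 1.12.

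A second simulation with different assumptions (true HR 1.25, control mean 30 days after the output, censoring at 180 days) shows the same pattern: 1.25 at f = 0, 1.19 at 20%, 1.15 at 40%, 1.12 at 50%.

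**Step 4: the 6-month exclusion.** If cases still undiagnosed at 6 months are removed rather than censored, the Step 3 settings lose 30% of at-risk controls but only 16.4% of at-risk intervention cases. Selection then depends on the outcome, and the slow cases that carry much of the contrast are lost. With true HR 1.5, simulation gives about 1.09 (f = 20%) or 1.02 (f = 40%) on all cases, and only about 1.14 to 1.17 on the at-risk cases. Moving the clock without also censoring these cases would recover little.

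**The case against.** **It is a secondary outcome, and its limits are acknowledged.** Multiple Hypothesis Testing treats secondary analyses as hypothesis generating. The sample size rests on confidence. The article also gives external influences, such as the wait for test results, as a reason not to make this outcome primary. This stands and lowers the severity. It does not remove the conflict, which the definition itself creates.

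**A later treatment may have been meant.** The Intervention section limits the study to cases without an established, confirmed diagnosis, so the authors may have intended only treatment begun afterwards. That is possible, but the text does not say so, and the earliest-event rule says otherwise.

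**The affected share may be small.** The fourth criterion is one of five routes in. This stands: f is unknown, and at 5% the dilution is slight.

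**A clock from the visit is a legitimate measure.** It is common to both arms and captures delay since presentation. This stands for description. For a treatment comparison, it mixes in time that the intervention could not affect.

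**Stronger readings.** A reader might infer that the outcome favours one arm or inflates type I error. Randomisation after the early events and within clinician rules that out in expectation. A reader might also infer that the outcome does not measure time to diagnosis at all. Two of its three components, a documented diagnosis and a confirmatory result, do. Finally, a reader might object that a wrong documented diagnosis counts as an event. The stated outcome is when the clinician established a diagnosis, and accuracy is a separate outcome. Requiring the adjudicated diagnosis would be a different estimand, not a correction.

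**Conclusion.** The conflict is established from the article's text alone. Empiric treatment that shows uncertainty at entry is scored as an established diagnosis, and events before randomisation count. The consequence is dilution of the hazard ratio toward 1 and lost power for the secondary outcome. There is no expected imbalance between arms and no effect on the primary outcome or its sample size. This is a should-fix.

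The size is not established. The share f, the true hazard ratio and the 70% diagnosed are all assumptions. Under them, with censoring at 6 months, a true 1.5 is estimated as about 1.35 (f = 20%) or 1.24 (f = 40%).

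It is tempting to quote a power gain: in the same illustration at f = 40%, 72% on all cases against 94% on those at risk. The documents do not support that as a promise. If the chart review exclusion applies to this outcome, which is the plain though not the only reading, the at-risk analysis has power of only about 27% in that setting.

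**What to change.** 1. Reconcile Primary and Secondary Outcomes with Case Selection Criteria, so that the empiric treatment that qualified a case is not a time-to-diagnosis event.
2. Start the clock at randomisation. The output exists for both arms at that point, so the origin is common. Analyse cases with no event before it. That set is defined by pre-randomisation facts, so the randomised comparison is preserved, provided the dates are coded without reference to arm.
3. For this analysis, censor cases undiagnosed at 6 months instead of excluding them.
4. Keep the visit-based time as a description, and report the number of cases with an event before randomisation, by arm. Time to the adjudicated final diagnosis could be a sensitivity analysis.

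**Cost.** Dates already read at chart review must be re-coded, and the analysis set shrinks by at most a fraction f: 132 of 660 cases at 20%, 264 at 40%. The loss is smaller to the extent that cases whose only early event was the qualifying treatment stay at risk. The Results section reports data collection complete as of June 2019, so this is a redefinition after collection. It should be dated, made before arms are compared on this outcome, and disclosed.
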